### 8.3 Statistical significance

The tests are two-sided, with the significance level set at 0.05. The statistical analysis will be conducted using STATA 14.0 or an updated version

### 8.4 Statistical analysis for stopping the research

No interim analysis is planned.

### 8.5 Missing or invalid data

Multiple imputation procedures will be performed on the data of patients involved in the principal analysis. We will address the problem of missing data using the state-of-the-art multiple imputation techniques, including all analysis variables, under the assumption that missing values are missing at random. Multiple imputation procedures will be conducted using the chained equation. We will estimate the fraction of missing information and apply the multiple imputation procedure, generating at least 50 imputed datasets. Analyses will run on each dataset and be pooled according to Rubin’s rules. We will compare the distributions of the observed, imputed, and completed values, and the post-imputation diagnostic plots will report the observed and completed values. We will use the kernel- Epanechnikov density estimator for continuous variables and a histogram for categorical variables. In addition, we will use the Kolmogorov- Smirnov statistics to compare the observed, and imputed distributions of each continuous imputed variable. The null hypothesis (i.e., observed and imputed data follow the same distribution) is rejected at  $P < 0.05$ . The imputed results will be presented as main results if they don’t differ from the complete case analysis estimates.

## **8.6 Substantive modifications to the research protocol**

If there is a need for changes to the original strategy analysis plan, a modification will be submitted to the CPP (Ethic Committee) in advance.

## **8.7 Patients included in the analysis**

Analysis populations will be :

- in intention-to-treat for the safety outcome (ITT: taking into account all randomized patients)
- in modified intention-to-treat analysis for the primary outcome (mITT: taking into account all randomized patients except those for which the eligibility criteria were not met)
- in Per-Protocol (PP: taking into account patients randomized but excluding the patients for which the eligibility criteria were not met and those who were declared free from any haemorrhagia after the hospital check-up.

All statistical analyses will be performed with STATA® software 14.0 or an updated version for Windows (STATA CORP LLC, College Station, Texas, USA).

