### **Data Analysis for the Secondary Endpoints:**

- The prehospital INR delta [between INR- management at the procedure site and INR-on arrival at the hospital] between the two groups will be studied with multilevel logistic regression modeling that will be fitted using a generalized estimating equation method to take into account time and both patient and hospital clustering. Where appropriate, this regression might be adjusted for unbalanced variables.
- The mean difference in fibrinogen levels between the two groups will be compared by a GEE model in the same way as for INR.
- The transfusion requirement will be compared by the number of blood products and plasma units transfused after arrival at the hospital, including packed RBCs, platelet concentrates, fibrinogen, coagulation factors, and Fresh frozen plasma. The transfusion requirement will be assessed at 6 and 24 h, taking the investigating center into account as a stratifying variable.
- The comparison of the median number of RBCs transfused between the two groups will use the Mann–Whitney U test
- The median number of days in the intensive care unit between the two groups will be studied overall and among surviving patients. They will be compared between the two groups by a Mann–Whitney U test.
- For each arm, actuarial survival will be visualized using the Kaplan–Meier estimator and compared with the log-rank test to estimate the effect of FLYP on survival. A multivariable Cox proportional hazard regression model may be fitted in cases of potential imbalance.
- The feasibility of administering FLYP will be judged by the responses to the CRF. page 9
- (Rate of positive responses to the various items)
- Safety outcome: The adverse event incidence will be compared between the two groups, using a Chi2 or a Fisher exact test.
- Exploratory subgroup analysis: we will report the effect size on the INR value in subgroups defined by variables of interest such as the type of injury, the prehospital vasopressor use, the prehospital intubation, the presence of a brain injury.
- Post-hoc analyses to further explain the primary outcome.  
We will measure, with an adapted model, the relationship between the INR value and the ratio of plasma-to-crystalloid volume, which seems to be an indicator of plasma dilution by superadded serum

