## 1584 **16.2   Objectives**

- 1585
- 1586                   ▪   Hypothesis
  - 1587                   ●   The null hypothesis is that there is no difference in the occurrence of trauma-induced
  - 1588                   coagulopathy between the standard and plasma groups. The alternative hypothesis is
  - 1589                   that there is a difference between the two groups.
- 1590                   ▪   Objectives
- 1591                   ▪   Principal
  - 1592                   ●   To show the effectiveness of FLYP administered prehospital during the management
  - 1593                   of hemorrhagic shock of traumatic origin, on the occurrence or treatment of post-
  - 1594                   traumatic coagulopathy.
- 1595                   ▪   Secondary
  - 1596                   ●   Feasibility of FLYP administration in the prehospital setting
  - 1597                   ●   Show that FLYP improves fibrinogen levels
  - 1598                   ●   To show that the contribution of FLYP decreases the transfusion needs (Red Blood
  - 1599                   Cells, plasma, coagulation factors, platelets)
  - 1600                   ●   To show that the contribution of FLYP decreases the length of stay in intensive care
  - 1601
  - 1602                   ●   Compare mortality between the two groups until D30
  - 1603                   ●   Validate the safety of plasma transfusion in the prehospital setting.

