## 1655   **Timing of outcome assessments**

- 1656                   ▪ The schedule of study procedures is given in paragraph 3.3.5 of the protocol.
- 1657                   The start time for each calculation is the participant's date of inclusion.

1658 **Confidence intervals and P values**

- 1659                   ▪ All statistical tests will be 2-sided and performed using a 5% significance level and 95% two-
- 1660                   sided confidence intervals.
- 1661                   ▪ No adjustment for multiplicity is planned
- 1662                   ▪ 95% two-sided confidence intervals

1663 **Adherence and Protocol deviations**

- 1664                   ▪ Protocol deviations are defined as:
- 1665                             ● Enrollment without meeting inclusion criteria
- 1666                             ● Incomplete or lack of patient consent
- 1667                   ▪ The number (and percentage) of patients with major and minor protocol deviations will be
- 1668                   summarized by treatment group, with details on the type of deviation. Protocol deviations will
- 1669                   be screened for in the intention-to-treat population.

1670 **Analysis populations**

- 1671                   ● The people analyzed will be:
- 1672                             ▪ for the safety outcome: all the randomized patients (intention-to-treat population).
- 1673                             ▪ for the primary and secondary outcomes: all the randomized patients except those who have an
- 1674                             exclusion criterion (modified intention-to-treat population)
- 1675                             ▪ for a sensibility analysis for the primary outcome: all the randomized patients except those who
- 1676                             have an exclusion criterion and those who finally have no bleeding after hospital assessment
- 1677                             (per-protocol analysis)

1678 **16.6 Trial Population**

- 1679                   ● Screening data
- 1680                             ▪ The number of patients screened will be reported for each investigating center. The flow chart
- 1681                             will note the total for all centers
- 1682                   ● Eligibility
- 1683                             ▪ The Consort Flow chart will report the number of patients eligible and not eligible due to an
- 1684                             exclusion criterion (paragraph 4· in the protocol)

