- 1685                   ● Recruitment, Withdrawal and Follow-up
- 1686                             ▪ The "CONSORT" diagram will report the number of people screened, eligible, consented,
- 1687                             randomized, receiving their allocated treatment.
- 1688                             ▪ The level of consent withdrawal will be tabulated as consent to continue follow-up and data
- 1689                             collection
- 1690                             ▪ Timing and number of patients lost to follow-up will be presented in a Kaplan-Meier Diagram.
- 1691                             ▪ The numbers of losses to follow-up will be summarized per treatment arm
- 1692                   ● Baseline patient characteristics
- 1693                             ▪ Patients will be described with respect to age, sex, comorbidities, type of injury, mechanism of
- 1694                             injury, anatomic localization of trauma, time response of advanced life support teams, vital
- 1695                             status at the point of injury (blood pressure, heart rate, shock-index, oxygen saturation),
- 1696
- 1697

1698 prehospital biological measures (Prothrombin time and INR value, hemoglobin and lactic acid  
1699 concentrations), body temperature, basic life support therapeutics, advanced life support  
1700 therapeutics, cumulated crystalloid volume, cumulated plasma volume, prehospital red cell  
1701 units transfused, vital signs on arrival at the intensive care unit (blood pressure, heart rate,  
1702 shock-index, injury severity score, traumatic brain injury confirmed with CT scan, laboratory  
1703 values - hemoglobin, platelets, lactic acid, base excess)

1704

- 1705     ▪ The description will be reported separately for the two randomized groups. Categorical data will
- 1706     be summarized by numbers and percentages. Continuous data will be summarized by mean, SD,
- 1707     and range if data are Gaussian, and median, IQR, and range if data are skewed. Tests of
- 1708     statistical significance will not be undertaken for baseline. Instead, the clinical importance of
- 1709     any imbalance will be noted.

1710

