### 1734 **Secondary endpoints**

- 1735     ▪ Comparison of fibrinogen changes by group: paired t-test, analysis of covariance
- 1736     ▪ Comparison of the volumes of blood loss, volumes infused or transfused, the quantity of amines
- 1737     used between the two groups (Chi2, Fisher's exact, Student's, Mann-Whitney tests).
- 1738     ▪ Comparison of the INR differential, delta INR : [INR at hospital admission - initial INR at the
- 1739     point of injury] between the two groups

- 1740                   ▪ We will compare the Delta-INR values between the plasma and control groups using a
- 1741                   linear mixed model with an independent covariance matrix, considering study group, time, and
- 1742                   Injury Severity Score levels as fixed effects and incorporating a random intercept.
- 1743                   ▪ Comparison of the length of stay in intensive care between the 2 groups : Student's t test, Mann-
- 1744                   Whitney test.
- 1745                   ▪ Number of days of hospitalization: Student's t-test, Mann-Whitney test
- 1746                   ▪ Survival analysis over the first 30 days: Kaplan Meier graphic, log-rank test.
- 1747                   ▪ Feasibility endpoint : listing of technical and logistical difficulties in plasma administration ,
- 1748                   number ad percentage of patients, number and percentage of plasma vials.
- 1749                   ▪ The analysis will all take into account a possible center effect.
- 1750                   ▪ Safety Endpoint is the occurrence of any of the following adverse events: thrombosis, allergic
- 1751                   symptoms, transfusion-related acute lung injury, and transfusion-associated circulatory
- 1752                   overload. The traceability of plasma, including prescription, delivery, and follow-up
- 1753                   procedures, will be assessed using the plasma follow-up sheet from the French Military Blood
- 1754                   Institute. The Health Defence Service will realize the qualitative and quantitative analysis of
- 1755                   Adverse Events. There is no formal statistical test preplanned
- 1756                   ▪ If the initial characteristics of patients are unbalanced between the two groups after
- 1757                   randomization, an adjusted analysis will be considered with a regression method. Where

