## 1799 **Harms**

- 1800                   ▪ The number of patients experiencing AE will be presented for each treatment arm.
- 1801                   ▪ For each patient, only the maximum severity experienced of each type of AE will be displayed.  
1802                   The number of occurrences of each AE will also be presented for each treatment arm. No  
1803                   statistical testing will be undertaken

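### Safety is defined only on all randomised patients, so any FLYP-arm patient given no plasma would dilute the rate of FLYP-caused reactions; a recipients-only table is missing.

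*Combined protocol and SAP*

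**What the plan says.** Protocol 8.7 sets the safety population as "in intention-to-treat for the safety outcome (ITT: taking into account all randomized patients". The SAP, under Analysis populations (within 16.5), agrees: "for the safety outcome: all the randomized patients (intention-to-treat population". The SAP's Harms section adds that "The number of patients experiencing AE will be presented for each treatment arm".

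The safety question itself concerns the product. SAP 16.2 lists among its aims to "Validate the safety of plasma transfusion in the prehospital setting". Under its secondary-endpoint methods the SAP states: "Safety Endpoint is the occurrence of any of the following adverse events: thrombosis, allergic" symptoms, TRALI and TACO.

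The one narrower set that might have served, per-protocol, is not based on exposure. Protocol 8.7 describes it as "excluding the patients for which the eligibility criteria were not met and those who were declared free from any haemorrhagia after the hospital check-up", and the SAP uses it only as a sensitivity analysis of the primary outcome.

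Receipt of plasma does appear elsewhere. The CONSORT diagram (SAP 16.6) will count patients "randomized, receiving their allocated treatment". The treatment given, any reaction to it and the time go into the CRF (protocol 3.9 and 5.4), and each plasma unit is traced (5.1.8). None of this is tied to a safety denominator.

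**The concern.** Study FLYP cannot cause an allergic reaction, TRALI or TACO in a patient who never received it. Such a patient, if kept in the FLYP-arm denominator, lowers the reported rate of product-caused reactions and tightens its upper confidence limit. For product harm, that error runs in the reassuring direction.

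The denominator matters because the SAP plans no formal test for the safety endpoint or for harms. There, the safety result is a set of descriptive counts and rates by arm.

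Non-receipt is conceivable from the documents. Protocol 3.3.1 lists FLYP after bleeding control, sampling and ventilatory support, and the powder must then be reconstituted. The CRF has a field for death before admission (3.9). The feasibility endpoint exists because problems in giving plasma were thought possible.

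**Working it through.** **Inputs**
- FLYP arm: 70 patients (protocol Summary and 8.2; SAP 16.5).
- f, the share of the FLYP arm given no study FLYP: not stated anywhere. Values of 0, 10, 20 and 30% are assumed.
- p, the event rate in recipients, and q, the event rate in FLYP-arm non-recipients: not stated. The values used are illustrative.

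**Step 1: the plan's denominator**

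With a difference of 0.3, SD 0.4, two-sided 0.05 and 80% power:
- n = 2 × (1.960 + 0.842)² × (0.4/0.3)² = 27.9, so 28 per group (29 with the t-test). The plan states 30.
- 30 / 0.5 = 60.
- 60 / 0.9 = 66.7, so 67, which the plan rounds up to 70.

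The figure of 70 is reproduced to within rounding. The 10% allowance is for missing consent, so it is not an estimate of f.

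**Step 2: reactions caused by study FLYP (q = 0)**

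The all-randomised rate is (1 − f) × p + f × q, which becomes (1 − f) × p when q = 0. With zero events the exact two-sided 95% upper limit on n patients is 1 − 0.025^(1/n).

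| f (assumed) | Recipients | A 5% recipient rate appears as | 3 events: of 70 / of recipients | 0 events, upper limit: on 70 / on recipients |
|---|---|---|---|---|
| 0 | 70 | 5.0% | 4.3% / 4.3% | 5.1% / 5.1% |
| 10% | 63 | 4.5% | 4.3% / 4.8% | 5.1% / 5.7% |
| 20% | 56 | 4.0% | 4.3% / 5.4% | 5.1% / 6.4% |
| 30% | 49 | 3.5% | 4.3% / 6.1% | 5.1% / 7.3% |

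The relative understatement equals f.

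**Step 3: events that can occur without study FLYP (q > 0)**

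Thrombosis needs no FLYP. Blood products given in hospital, which include plasma (protocol 8.1), can cause allergic symptoms, TRALI or TACO in either arm. With p = 5% and f = 20%:
- q = 0: 0.8 × 5% + 0.2 × 0% = 4.0%
- q = 5%: 0.8 × 5% + 0.2 × 5% = 5.0%
- q = 10%: 0.8 × 5% + 0.2 × 10% = 6.0%

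The all-randomised rate may therefore lie below, at or above the recipients' rate. The (1 − f) rule does not carry over to the whole four-part endpoint.

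**The case against.** The strongest reply has four parts.

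- **Non-receipt may be rare.** Each vehicle carries one study package, which is opened only at the moment of use (protocol 5.5). Reconstitution takes about six minutes at most (1.4, 5.1.3). Bottles already connected stay with the patient (3.3.1), so a patient who arrives early can still count as exposed. The CONSORT count of patients who received their allocation is standard reporting; a reader might infer from it that the plan expects a mismatch, but it does not predict one. This stands.
- **A reader could divide by hand.** The CONSORT diagram gives a count of those treated, and reactions to administration are recorded. This stands in part. The documents do not say what counts as receiving the allocation (any volume, for instance), and no recipient rate or limit is prespecified. The monitoring committee's causality review (7.5) is case review rather than a rate. The SAP also assigns an adverse-event analysis to the Health Defence Service but names no denominator for it.
- **The plan specifies no single-arm limit for safety.** True. The SAP has only a general rule of two-sided 95% intervals, so the limits above show precision; they do not restate a planned result.
- **All-randomised analysis protects the comparison.** A reader might infer that safety should be analysed as any FLYP versus none. The documents do not support that. FLYP-arm non-recipients, who may include early deaths and early arrivals, would move into the comparator. That could load severe outcomes onto the no-plasma group and make FLYP look safer. This stands in full and limits the remedy to a supplementary table.

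**Conclusion.** The gap is real but conditional. Both documents define only an all-randomised safety set, so there is no prespecified rate of reactions among patients who actually received study FLYP. If f is above zero, the rate of FLYP-caused allergic symptoms, TRALI and TACO is understated in relative terms by f.

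A reader might go further and conclude that the plan does understate plasma harm. The documents do not show this: they give no f, and the kit procedures suggest it could be small. At f = 0 nothing is lost. At an assumed 10 to 20%, the zero-event upper limit moves from 5.1% to between 5.7% and 6.4%. For thrombosis and reactions to in-hospital products, no direction can be claimed.

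This is a worthwhile, inexpensive improvement to the safety reporting. The between-arm comparison on all randomised patients remains valid.

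**What to change.** 1. Keep the all-randomised table as the between-arm safety comparison.
2. In protocol 8.7, the SAP's Analysis populations (16.5) and Harms, define a supplementary set: FLYP-arm patients who received any volume of study FLYP.
3. On that denominator, report allergic symptoms, TRALI and TACO, each with an exact two-sided 95% interval, and state how many FLYP-arm patients received none.
4. State the denominator of the Health Defence Service analysis.
5. Do not replace the randomised comparison with any FLYP versus none.

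Two neighbouring passages should be reconciled in the same edit. Protocol 8.1 says "The adverse event incidence will be compared between the two groups, using a Chi2 or a Fisher exact test", while the SAP plans no testing of harms. Protocol 4.4 says data from patients who withdraw will not be used, which does not fit a safety set of all randomised patients.

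**Cost:** one definition and one descriptive table from data already collected. The table is not a randomised comparison and does not by itself separate reactions to FLYP from reactions to later hospital products, so it should be labelled supportive. If every FLYP-arm patient received plasma, its denominator matches that of the all-randomised FLYP arm.

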# **9 RIGHT OF ACCESS TO SOURCE DATA AND DOCUMENTS**

The sponsor has obtained the agreement of all parties involved in the research to ensure direct access to all research sites, source data, source documents, and reports for quality control and audit purposes by the sponsor.

The investigators will make available the documents and individual data strictly necessary for the follow-up, quality control, and audit of the biomedical research to the persons mandated by the sponsor following the legislative and regulatory provisions in force (articles L.1121-3 and R.5121-13 of the public health code).

Any original document or object that proves the existence or accuracy of a data or fact recorded during the research is defined as a source document.

Access to data will be limited to those who need access to perform their tasks.

## **9.1 Privacy and Confidentiality**

Following the legislative provisions in force (articles L.1121-3 and R.5121-13 of the Public Health Code), persons with direct access to the source data will take all necessary precautions to ensure the confidentiality of information relating to the investigational medicinal products, to the research, to the persons involved, and in particular with regard to their identity and the results obtained. Furthermore, these persons, as well as the investigators themselves, are subject to professional secrecy.

During the biomedical research or at its conclusion, the data collected on the persons who lend themselves to it and transmitted to the sponsor by the investigators (or any other specialized intervening parties) will be made anonymous. Under no circumstances must the names of the persons concerned or their addresses appear in clear text.

The sponsor will ensure that each person who participates in the research has given written consent for access to their data that is strictly necessary for the quality control of the study.

If the participant is included on an emergency basis, in the absence of signed consent (from the family, the trusted person, the patient in the case of consent to continue the study), the principal investigating physician at each center will answer questions from personnel mandated by the sponsor for monitoring, based on the medical record. Direct access to medical data by persons mandated by the sponsor will not be possible without the signature of a consent form.

